### Study endpoints

#### Epidemiological

Primary endpoint: the cumulative incidence of malaria parasitaemia (asymptomatic and symptomatic) defined as the number of mRDT-confirmed episodes of parasitaemia per child per year. A child will be considered to have experienced an episode of parasitaemia during a given month if they had a positive mRDT during the scheduled monthly follow-up visit, irrespective of symptoms. Two consecutive positive scheduled mRDT results will be treated as two separate episodes and any malaria cases diagnosed and treated at health facilities between monthly visits will also be counted as episodes.

Secondary endpoints: (i) time to first episode of malaria parasitaemia (asymptomatic and symptomatic) as determined by mRDT as per the primary case definition; (ii) changes in mean levels of haemoglobin among cohort children aged 6 to 59 months.

All study outcomes will be compared between the intervention (ITWL + LLINs) and the control arm (LLINs only).

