Active monthly follow-ups will occur at village sentinel sites. CHWs will be responsible for organizing village leaders and parents in advance of the scheduled visit, including arranging for school-aged children to be monitored outside school hours. At each follow-up, the clinical team will administer a physical examination, as described above, and record a short medical history to assess recent febrile illness, LLIN use and health care-seeking behaviour. A blood specimen will be collected by finger-prick for an immediate mRDT; anaemia (moderate: haemoglobin 7–8 g/dl to severe: haemoglobin <7 g/dl) will be measured in children aged 6 to 59 months at enrollment, at 6 months and 1 year post-intervention. In the case of a positive mRDT, the child will receive a curative weight-appropriate course of ALU, unless the child is already taking an appropriate antimalarial or has been within the past 2 weeks.

During the course of the study, the clinical team will also provide treatment for non-malaria illnesses, including paracetamol if axillary temperature is ≥37.5 °C, amoxicillin for non-severe pneumonia, oral rehydration salts (ORS) plus zinc for gastroenteritis and ferrous sulphate plus albendazole for anaemia (haemoglobin <9 g/dl). Children with severe illness at any time will be referred to Teule district hospital for further management. Participants are also free to receive medication from health personnel outside of the study teams.

Enrolled cohort children will be provided separate study booklets that their parents or guardians will be instructed to present each time that their child visits a health facility during the follow-up period. The 24 health facilities serving the study area will be visited by the study teams prior to the start of the study. Healthcare workers will be trained to properly complete the study booklet for enrolled children, recording whether the child was tested for malaria either by microscopy or mRDT during the visit, the result of the test, and what medication was prescribed or administered. During the monthly follow-up visits, study teams will ask parents or guardians of enrolled cohort children to present the study booklets, and any data on interim health facility visits will be collected electronically. Parents and guardians will also be asked to describe any other illness episodes that were not recorded in the study booklet.

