### Data analysis

All statistical analyses will be performed using STATA version 13 (StataCorp LP, College Station, TX, USA). The primary endpoint will be a comparison of the cumulative incidence of symptomatic or asymptomatic episodes of malaria in children between the two intervention groups. Data from cohort members who are lost to follow-up or who missed monthly visit(s) will be treated as censored. Similarly, children who are taking anti-malarial drugs, based on a positive mRDT, will be excluded in the analysis for the first 2 weeks following treatment. History of travel away from the study village will be recorded during monthly visits and time at risk will be censored for such periods. In addition, malaria cases in children who resided outside their cluster area for more than half of the elapsed study period at the time of illness will be excluded.

An initial analysis will compare the cumulative malaria incidence rates between the two study arms to assess the number of episodes of malaria parasitaemia (symptomatic, asymptomatic or combined) per child per year. A follow-up analysis will examine the time to first episode of clinical malaria. The rate ratio (RR) will be calculated by dividing the incidence rate in the intervention relative to the control arm. The effectiveness of ITWL + LLINs vs. LLINs alone will be obtained from the final analysis as 1-RR. Cox regression modeling will be used to investigate potential confounding such as season and age. A priori confounders will be included in the model and that the presence of effect modification or interaction terms will be explored. Both intention to treat (all persons randomized) and per protocol analyses (all persons who received the intervention) will be conducted. All analyses will be adjusted for within-cluster correlation using generalized estimating equations or random effects models with gamma frailty. In addition, missing data will be analyzed and multiple imputation used, if required.

Similarly, mean haemoglobin in 6–59 month olds will be measured and compared between the two arms.

Other outcome variables, including entomological indices, cost-effectiveness and acceptability of interventions will be compared between study arms accounting for any correlated observations within clusters or households.

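### The primary endpoint is labelled mRDT-confirmed, but its counting rule admits health-facility malaria cases without any positive test

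*Protocol article*

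**What the plan says.** Four places in the protocol article bear on this point.

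- **Study endpoints, Epidemiological, primary endpoint.** Cumulative incidence is "defined as the number of mRDT-confirmed episodes of parasitaemia per child per year". The same paragraph adds that "any malaria cases diagnosed and treated at health facilities between monthly visits will also be counted as episodes". The second statement names no test and no result.
- **Study endpoints, Epidemiological, secondary endpoint (i).** Time to first episode is "as determined by mRDT as per the primary case definition".
- **Clinical evaluations and patient treatment.** Facility staff complete a booklet "recording whether the child was tested for malaria either by microscopy or mRDT during the visit, the result of the test", and also the medication prescribed or given. Study teams collect these entries electronically at the monthly visits.
- **Data analysis.** The post-treatment rule is that "children who are taking anti-malarial drugs, based on a positive mRDT, will be excluded in the analysis for the first 2 weeks following treatment".

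**The concern.** The definition and the counting rule cannot both be followed. Under the definition, a facility case counts only with a positive mRDT. Under the rule, being diagnosed and treated is enough. The booklet asks whether a test was done and allows two kinds of test, so the protocol itself expects facility visits with no test or with microscopy only.

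A fever treated as malaria without a test may not be malaria, and wall lining would not prevent it. Such events add to both arms without carrying any treatment effect. Facility diagnosis is also outside the study team's control, and Randomization and blinding states that installation cannot be blinded because the lining is plainly visible. If care-seeking or presumptive treatment differs by arm, the error is no longer a simple dilution. At stake are the primary rate ratio, the effectiveness estimate (1 − RR) and the time-to-first-episode comparison, where a single unconfirmed case can be the event.

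**Working it through.** **1. The plan's own power figure.** Inputs from Sample size rationale, Epidemiological:

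- c = 22 clusters per arm.
- 110 children less 18 % loss: 110 × 0.82 = 90.2, so y = 90 child-years per cluster.
- CV k = 0.302.
- λ0 = 2.5 (range 2.5–3.0) and a 30 % reduction, so λ1 = 1.75.
- 5 % significance, taken as two-sided because the article does not say.

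Hayes–Bennett formula, solved for power:

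Power = Φ( √[(c − 1)(λ0 − λ1)² / V] − 1.96 ), with V = (λ0 + λ1)/y + k²(λ0² + λ1²).

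V = 4.25/90 + 0.0912 × (6.25 + 3.0625) ≈ 0.047 + 0.849 ≈ 0.897. Then √(21 × 0.5625/0.897) = 3.63, and Φ(3.63 − 1.96) = Φ(1.67) ≈ 95 %. With λ0 = 3.0 the result is also about 95 %. The stated power of more than 85 % is met with room to spare.

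**2. Who is counted under each reading**

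| Facility visit | Definition (mRDT-confirmed) | Counting rule (diagnosed and treated) |
|---|---|---|
| mRDT positive, treated | counts | counts |
| Microscopy positive, treated | does not count | counts |
| No test, treated as malaria | does not count | counts |

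The last two rows are where the text conflicts with itself.

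**3. Equal rates of unconfirmed cases in both arms.** The article gives no such rate, so u per child-year is an assumption. Observed RR = (1.75 + u)/(2.5 + u). Power uses the formula above with both rates raised by u and k held at 0.302.

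| u | RR | Power |
|---|---|---|
| 0.1 | 1.85/2.60 = 0.712 | 93.5 % |
| 0.3 | 2.05/2.80 = 0.732 | 89.3 % |
| 0.5 | 2.25/3.00 = 0.750 | 84.3 % |

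For u = 0.5: V = 5.25/90 + 0.0912 × (9 + 5.0625) = 0.058 + 1.283 = 1.341; √(21 × 0.5625/1.341) = 2.968; Φ(1.008) = 84.3 %. With λ0 = 3.0 and u = 0.5, RR = 2.6/3.5 = 0.743 and power is 86.7 %, still above 85 %.

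The power loss depends on applying k = 0.302 to the enlarged count. If unconfirmed cases occurred at the same rate in every cluster, the between-cluster term would stay at 0.849. At u = 0.5, V would be 0.058 + 0.849 ≈ 0.908 and power Φ(3.607 − 1.96) ≈ 95 %. The shift in the RR is the same in either case.

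**4. Unequal rates (assumed for illustration).** With 0.3 in control and 0.1 in intervention, RR = 1.85/2.80 = 0.661, which overstates the effect. With 0.1 in control and 0.3 in intervention, RR = 2.05/2.60 = 0.788, which understates it.

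**5. The 2-week exclusion.** Suppose a child is treated at a facility 8 days before a scheduled visit and has a positive mRDT at that visit. If the facility treatment followed a positive mRDT, the visit falls inside the excluded 2 weeks. If it followed microscopy or no test, the exclusion as worded does not apply and both events count.

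**The case against.** The strongest reply is that the lead definition governs, and that diagnosed should be read as test-positive, since the booklet is built around tests. That reading is reasonable for untested cases. It leaves microscopy-positive cases outside an mRDT-only definition, and the word any points the other way. Two analysts could follow the text faithfully and count differently.

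A second reply is that the harm is small. That largely stands. The article gives no rate of unconfirmed cases, power stays above 85 % until that rate approaches 0.5 per child-year, and whether it falls below depends on how the CV behaves. Nor does the article say that facility staff know a child's arm, only that installation cannot be blinded.

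A reader might go further and infer that "Two consecutive positive scheduled mRDT results will be treated as two separate episodes" is itself an error. The documents do not support that. It is an explicit choice, and the planning rate of 2.5–3.0 detected episodes is close to 12 times the 22–25 % baseline prevalence (2.64–3.0), so the 30 % target appears to be set on the same scale. No section says that a test stays positive after treatment. Requiring a negative test between episodes, without also removing time at risk, would do harm. With monthly risks p of 2.5/12 and 1.75/12 and no lingering positivity, p + 11p(1 − p) gives 2.02 versus 1.52 episodes: RR 0.75, and a difference of about 0.51 where the true one is 0.75.

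A reader might also infer that unconfirmed cases inflate the cases averted in the cost-effectiveness analysis. Under equal rates they do not: (2.5 + u) − (1.75 + u) = 0.75 for every u. The article also does not say that the primary count feeds that analysis.

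**Conclusion.** The point holds as an inconsistency in the primary case definition, with a matching gap in the post-treatment exclusion. Facility cases without a positive test can enter an endpoint labelled mRDT-confirmed, and also the time-to-first-episode endpoint that depends on it.

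Under equal, assumed rates of 0.1–0.5 per child-year, a true rate ratio of 0.70 would be observed as 0.71–0.75. Power would fall from about 95 % to between 93.5 % and 84.3 % at a control rate of 2.5, with the CV held at 0.302. Under unequal rates the direction is open. These rates illustrate the possible size; the documents do not provide them. The contradiction in the text does not depend on them. The point does not extend to consecutive positive scheduled tests or to cases averted.

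**What to change.** In Study endpoints, Epidemiological:

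- Count a facility case as an episode only if the booklet documents a positive mRDT or microscopy result.
- Amend the primary definition and secondary endpoint (i) so that both accept either test.
- Name a sensitivity analysis that adds treated facility cases without a documented positive result.

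In Data analysis, apply the existing 2-week exclusion from the analysis after any recorded antimalarial treatment, however the case was diagnosed. The rule for counting scheduled positives can stay as it is.

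The cost is wording only, because test, result and medication are already recorded in the booklet. A few true cases without a recorded test will be lost from the primary count; the sensitivity analysis shows whether that matters.

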### Secondary objectives

#### Epidemiological

To assess the effectiveness of ITWL + LLINs compared to LLINs alone, on time to first episode of malaria (asymptomatic and symptomatic) in children aged 6 months to 11 years old.To assess the effectiveness of ITWL + LLINs compared to LLINs alone, on mean haemoglobin concentration in children aged 6 to 59 months old.

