### Sample size rationale

#### Epidemiological

LLINs can reduce malaria morbidity by approximately 40–70 % [3]; the impact of ITWL alone or in combination with LLINs on malaria is unknown. The effects may be additive or synergistic (e.g. by having a mass killing effect and/or reducing mosquito longevity) or antagonistic (e.g. if the LLINs are repellent thereby reducing mosquito house entry and contact with ITWL). Due to the intensity and projected cost of the ITWL intervention, a minimum reduction in malaria of 30 % is considered of public health importance.

For the cohort study, sample size is based on annual cumulative incidence of malaria infection in each study arm as the primary outcome. From baseline surveys conducted in Muheza, it was assumed that cumulative incidence of malaria would be 2.5–3.0 detected episodes/year, with a coefficient of variation (CV) between clusters of 0.302 and an intra-cluster correlation (ICC) of 0.047. Therefore with 22 clusters per arm, sampling an average of 110 children (assuming 18 % loss to follow-up) per cluster, the study will have >85 % power to detect a 30 % reduction in malaria incidence at the 5 % significance level [59].

To measure time to first malaria episode during the evaluation year, assuming an ICC of 0.047, for a cumulative incidence of 2.0 episodes/year, the monthly risk would be 0.167. Using a binomial distribution calculation, the probability of having zero positive determinations (i.e. of ‘surviving’ malaria-free) over 1 year is (1–0.167)^12^ = 0.112; with a monthly 30 % reduction in risk, the cumulative probability of having no monthly positive RDTs in 12 months in the intervention arm would be (1–0.117)^12^ = 0.226. Sampling from 44 clusters with 90 children per cluster, the study will have 99 % power to reject the null hypothesis of no difference in ‘survival’.

To assess the effectiveness of the interventions on anaemia in children aged 6 to 59 months, assuming mean haemoglobin of 10.75 g/dl, 22 clusters in each study arm and a CV of 0.048, the study will be able to detect a difference of 0.5 g/dl in mean haemoglobin with 5 % significance and 85 % power between the study arms, sampling an average of 45 children per cluster.

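### The haemoglobin endpoint is worded as a change, but the objective, power and analysis use a mean at an unnamed visit; state one baseline-adjusted follow-up comparison throughout

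*Protocol article*

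**What the plan says.** The protocol article gives this outcome in two forms.

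- **Change.** Study endpoints, Epidemiological: "changes in mean levels of haemoglobin among cohort children aged 6 to 59 months".
- **Mean.** Secondary objectives, Epidemiological: the effect is assessed "on mean haemoglobin concentration in children aged 6 to 59 months old". Sample size rationale, Epidemiological: "the study will be able to detect a difference of 0.5 g/dl in mean haemoglobin", with the inputs "assuming mean haemoglobin of 10.75 g/dl, 22 clusters in each study arm and a CV of 0.048" and "sampling an average of 45 children per cluster". Data analysis: "mean haemoglobin in 6–59 month olds will be measured and compared between the two arms".

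Enrolment values will exist. Under Clinical evaluations and patient treatment, anaemia, defined there by haemoglobin, "will be measured in children aged 6 to 59 months at enrollment, at 6 months and 1 year post-intervention". The only use stated for baseline haemoglobin is under Randomization and blinding, where it serves to check how far villages differ in disease burden before monitoring starts. The same section accepts that, with few units randomized, the arms may differ by chance. No section says whether the between-arm comparison is made at 6 months, at 1 year or over both.

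**The concern.** A change from enrolment and a mean at follow-up lead to different tests on the same data. Under randomization both estimate the same expected difference between arms, but their variances differ and they treat baseline imbalance differently. A follow-up mean with no adjustment carries part of any chance imbalance into the estimate. A change score subtracts all of it, which over-corrects when the correlation is modest.

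Two forms of the outcome and two possible visits leave at least four candidate analyses for an endpoint that has its own power statement. That statement can apply to only one form. An analysis plan can add detail to a protocol, but it should not have to choose between an endpoint definition and an analysis section that disagree.

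**Working it through.** **Inputs from the Sample size rationale.** Control mean 10.75 g/dl; 22 clusters per arm; between-cluster CV k = 0.048; m = 45 children per cluster; difference d = 0.5 g/dl; 5 % significance (two-sided assumed); 85 % power. The within-cluster SD of a child's haemoglobin, s, is not given and is varied.

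**Step 1: reproduce the stated power.** For two means in a cluster trial:

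c = 1 + (z_α/2 + z_β)² [2s²/m + k²(μ0² + μ1²)] / d²

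Solving for power gives Φ(d/SE − 1.96), with SE² = [2s²/m + k²(μ0² + μ1²)]/(c − 1).

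Worked case: μ1 = 11.25 and s = 1.0. The between-cluster term is 0.002304 × (115.56 + 126.56) = 0.558 and the within-cluster term is 2/45 = 0.044. Then SE = √(0.602/21) = 0.169, and power = Φ(2.95 − 1.96) = 84.0 %.

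| s (g/dl) | effect upward (11.25) | effect downward (10.25) |
|---|---|---|
| 0 | 86.6 % | 89.5 % |
| 0.8 | 84.9 % | 87.8 % |
| 1.0 | 84.0 % | 86.9 % |
| 1.3 | 82.1 % | 85.1 % |
| 1.5 | 80.6 % | 83.6 % |

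The stated 85 % is therefore consistent with a comparison of means at one time point. Exactly 85 % needs s of about 0.78 (upward) or 1.31 (downward). No correlation or SD of change enters.

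**Step 2: which correlation matters.** The between-cluster SD is 0.048 × 10.75 = 0.516 g/dl, variance 0.266. Taking s from 1.0 to 1.5, the within-cluster part of a cluster mean's variance is s²/45 = 0.022 to 0.050. The between-cluster share is 0.266/(0.266 + 0.022) = 92 % down to 0.266/(0.266 + 0.050) = 84 %. Power therefore depends mainly on r, the enrolment/follow-up correlation of cluster means. A modest correlation between individual children's values would not by itself make r modest.

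**Step 3: power of the alternatives.** With equal variances at the two visits, the variance relative to the follow-up mean is 2(1 − r) for change and 1 − r² for the baseline-adjusted comparison. Taking the planned 85 % as the starting point:

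power = Φ((1.960 + 1.036)/√factor − 1.960)

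The value of r is an assumption, so a range is shown.

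| r | change score | baseline-adjusted |
|---|---|---|
| 0.2 | 66 % | 86 % |
| 0.3 | 72 % | 88 % |
| 0.4 | 78 % | 90 % |
| 0.5 | 85 % | 93 % |
| 0.6 | 92 % | 96 % |
| 0.7 | 97 % | 99 % |

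Check at r = 0.3: the change factor is 1.4, 2.996/1.183 = 2.53, and Φ(0.57) = 72 %. Holding 85 % with change scores at that r would need 22 × 1.4 = 30.8, or 31, clusters per arm.

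**Step 4: likely size of baseline imbalance.** If enrolment cluster means vary as planned, the between-arm difference at enrolment has an SE of at least √(2 × 0.266/22) = 0.16 g/dl, about three tenths of the 0.5 g/dl target. This ignores any gain from stratifying on malaria prevalence.

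**The case against.** The best defence is that only one phrase is out of line. It speaks of changes in mean levels, which may be loose group-level language and not a child-level change score; the objective, power and analysis all agree on the mean. This carries weight: the fault is one of wording. But the phrase sits in the endpoint definition, the visit is named nowhere, and the ambiguity itself needs resolving.

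Three stronger readings are tempting, and the documents do not support them.

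- **That the trial is underpowered for haemoglobin, or that the 85 % is wrong.** It is neither shown nor implied. The figure is consistent with the comparison that three of the four sections describe. A loss arises only if change scores are used and r is below 0.5; above 0.5 they gain power. Treatment of all children at enrolment, and of anaemia during the study, might weaken the correlation, but that is inference and does not place r below 0.5.
- **That not naming enrolment haemoglobin as a covariate is an error.** A journal article commonly leaves covariates for a secondary endpoint to the full protocol or analysis plan, which are not shown. The covariate is part of the remedy and not the defect.
- **That the plan commits to raw, unadjusted follow-up means.** It does not say so. The Data analysis section links the haemoglobin comparison to a preceding paragraph that applies clustering adjustment to all analyses and includes prespecified confounders in its Cox model. That does not establish adjustment for enrolment haemoglobin, but nothing excludes it.

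**Conclusion.** The point holds as an inconsistency in the stated estimand. The endpoint is a change in one section and a mean in three, with no visit named, and the power statement covers only the mean. The consequence for power is conditional: for change scores, from about 66 % at r = 0.2 to 97 % at r = 0.7, with 85 % reached at r = 0.5. The figures rest on a two-sided 5 % test, equal variances at the two visits, a large-sample approximation, and an r for cluster means that the documents do not supply.

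Baseline adjustment is at least as precise as either stated form across this range. Its gain over the plain mean is small at low r (about 1 point at 0.2) and about 8 points at 0.5. The case for it is that it replaces two conflicting forms with one analysis at almost no cost, not that the planned comparison is invalid.

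**What to change.** In Secondary objectives, Study endpoints, Sample size rationale and Data analysis, state the same estimand: the between-arm difference in haemoglobin at one named follow-up visit, in children aged 6 to 59 months. Remove the reference to changes. Analyse it in a linear model that allows for clustering, with enrolment haemoglobin as covariate, entered both as the child's value and as the cluster mean. The cluster mean is needed because most of the variance of the comparison lies between clusters.

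In the Sample size rationale, keep the 85 % and say that it is for a comparison of means at that visit without allowance for baseline adjustment.

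The cost is wording in four places and one or two of the 2 × (22 − 1) = 42 cluster-level degrees of freedom. No further data are needed, because enrolment haemoglobin is already collected.
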